### Recruitment {15}

All new patients presenting to participating EDs and triaged by nurses (based on the usual triage process used in each ED) as having a possible MSKD will be considered for this study. In addition, a research professional in each site will screen the triage lists to identify any other potential participants for the trial and ensure none are omitted. Eligibility of ED patients will subsequently be assessed regarding the inclusion and exclusion criteria during an in-person interview with a research professional and review of medical records. Research professionals will explain the study to eligible patients and obtain their informed consent.

For patients who decline participation in the project, demographic data, such as age, sex, reason for consultation, and reason to refuse to participate, will be collected to calculate participation proportions and establish comparisons between participants and non-participants.

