#### Intervention description {11a}

The experimental arm will receive APP-led care. Patients will be independently managed (assessment and intervention) by a PT (*n* = 12, two per site). The PT will make a diagnosis and initiate an intervention plan (e.g., education and exercise). If relevant, the PT will make recommendations for medical imaging tests or medication. PTs will also recommend the proper discharge from the ED, such as hospitalization, discharge without medical consultation/follow-up, or discharge with a medical follow-up or rehabilitation in an outpatient setting. To ensure that these medical recommendations made by PTs in respect of the current professional legislations, an independent ED physician, not participating in the usual care arm, will be present in the ED and will be available to ensure the required medical care according to the PTs intervention plan (e.g., prescribe medication/tests/referrals) if needed. In the event that modification to the plan is found necessary (i.e., only if found unsafe for the patient) by the independent ED physician, this will be recorded and secondary analyses including only participants with no plan modifications will be performed.

The control arm will receive the usual ED physician care delivered by an ED physician. This will include independent assessment, treatment, and discharge by an ED physician with no physiotherapy within the ED but a physician’s referral to outpatient physiotherapy or other professionals/medical specialists will be possible. Overall care offered by the ED physician will not be standardized but will be systematically documented.

Participants in both arms presenting a non-MSKD condition after assessment will be excluded from the study. The proportion of excluded participants per group, as well as the reasons for exclusion, will be systematically collected and analyzed (Fig. 1).

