#### Wait to initial assessment and ED length of stay measures

Wait in the ED, which is defined as the time between the arrival in the ED and the initial evaluation by a physician or a PT will be recorded. The total length of stay in the ED will also be recorded in minutes by research professionals onsite.

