
### Strength and limitations

This study is the first multicenter pragmatic trial with a cost analysis assessing APP-led ED care. The trial has been designed by a group of experts with expertise in the management of MSKD, public health, epidemiology, cost analyses, health services, ED medicine, interprofessional collaboration, rehabilitation, and designing and performing RCTs. The stepped-wedge design is an emerging and original methodology that facilitates the evaluation and implementation of new models of care [67].

Although this trial is a pragmatic design, because of its experimental nature, it may not fully represent usual care that APPTs or ED physicians offer as they are aware of the objective of the trial. Moreover, patients are not blinded to providers that will offer care, and it may influence their perceptions. Still, this approach is necessary because of the pragmatic nature of the proposed trial, and it is important that patients know which provider and models of care they are exposed to as this increases the external validity of the current trial. Also, only a limited number of APPTs (12) will be assessing patients within this study across six EDs across Canada.

While APP-led ED models of care are emerging globally, none of these models has been evaluated across Canada where these models are also becoming more prominent. MSKD not only represent a significant economic burden for Canadians, but also have a significant impact on population health, the Canadian workforce, and our health care system. As such, new models of care that result in more efficient care are needed. Given the high consultation rates for MSKD and known overcrowding in EDs, this trial has the potential to improve access and efficiency of ED care.

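### Recruitment hours are not tied to physiotherapist cover in control periods, so wait and length of stay may be confounded by arrival time

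*Protocol article*

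**What the plan says.** Recruitment {15} starts from "All new patients presenting to participating EDs and triaged by nurses" as possibly having a musculoskeletal disorder. It adds that a research professional at each site will "screen the triage lists to identify any other potential participants for the trial and ensure none are omitted". Eligibility is then settled "during an in-person interview with a research professional and review of medical records". The section gives no days or hours and does not distinguish control from APP periods.

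Intervention description {11a} says of the experimental arm: "Patients will be independently managed (assessment and intervention) by a PT". It allots two physiotherapists to each site, 12 in all. It also requires an independent ED physician, from outside the usual care arm, to be in the department for care that the physiotherapist may not order. The control arm needs only usual ED physician care. Strength and limitations acknowledges that "only a limited number of APPTs (12) will be assessing patients within this study across six EDs across Canada".

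The fourth objective compares wait and ED length of stay. Wait is "the time between the arrival in the ED and the initial evaluation by a physician or a PT". On length of stay: "The total length of stay in the ED will also be recorded in minutes by research professionals onsite".

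Statistical methods {20a} plans a linear mixed model with a random cluster effect and fixed effects for intervention status and period. Adjustment is foreseen if baseline differences are seen. The baseline variables listed under Outcomes {12} do not include arrival hour or weekday.

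**The concern.** The recruitment frame is the same in every period, but the conditions for delivering care are not. In a control period an eligible patient can be enrolled whenever a research professional is on site and an ED physician is working. In an APP period the same patient can receive the assigned care only if a physiotherapist and the independent physician are also there. Two physiotherapists cannot staff an ED continuously. The feasible window can therefore be narrower after a site's switch than before it, and the article has no rule that makes the two equal.

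This needs no biased recruiter; it can follow from the roster alone. Wait and length of stay plausibly depend on the hour and day of arrival. If enrolled hours change at the switch, part of the estimated difference on the fourth objective would be a time-of-day effect attributed to the model of care.

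**Working it through.** **1. Accrual figures, reproduced.** From Trial design {8} and Sample size {14}: 6 sites, 4 periods of 6 weeks, 31 patients per site per period.
- 31 × 4 × 6 = 744, and 744 / 6 = 124 per site, as stated.
- Half of the 24 site-periods are APP, so 12 × 31 = 372 patients are planned in each condition.
- The 27 analysable patients per site-period also reproduce. A stepped-wedge (Hussey–Hughes) calculation with effect 0.35, ICC 0.004 and two-sided 0.05 gives power 0.800 at 27 and 0.787 at 26. The present point does not affect this figure.

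**2. Is a restricted window feasible?**
- 31 / 6 = 5.2 patients per site per week
- 31 / 30 = 1.03 per weekday
- 31 / (6 × 2) = 2.6 per physiotherapist per week

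These rates can plausibly be met in limited hours in both conditions.

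**3. How much of the week can two physiotherapists cover?** The article gives no shift lengths. Assuming 37.5 hours a week each, cover is 75 / 168 = 45% of the week with no overlap and 37.5 / 168 = 22% with full overlap. This shows only that cover is partial. It does not show when control patients are enrolled.

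**4. Would the planned model absorb a change in hours?** For site i and period j, let X = 1 in APP periods and 0 in control periods. Let q be the share of control-period patients arriving outside physiotherapist hours, with none in APP periods. Let D be the off-hours difference in mean wait, and θ the true effect. Then

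E(Y) = μ + αᵢ + βⱼ + θX + qD(1 − X) = (μ + qD) + αᵢ + βⱼ + (θ − qD)X.

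The site effects αᵢ and period effects βⱼ are untouched. The whole of qD moves into the coefficient of X, because the shift follows the same pattern as the intervention. If APP periods have an off-hours share q₁ and control periods q₀, the bias is −(q₀ − q₁)D. Equal shares give zero. The same algebra applies to length of stay.

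**5. Illustrative size.** The article gives neither q nor D; both are assumed. The table shows the shift in control mean wait, q × D, in minutes.

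| q | D = 30 | D = 60 |
|---|---|---|
| 0 | 0 | 0 |
| 0.1 | 3 | 6 |
| 0.3 | 9 | 18 |
| 0.5 | 15 | 30 |

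A negative D reverses the sign, so the bias could favour either model of care.

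**6. Does the planned adjustment cover it?** The comparison that triggers adjustment is of baseline demographic data, and arrival hour and weekday are not listed. Arrival time must nevertheless be recorded, since wait is measured from it.

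**The case against.** The strongest reply is that the article never says patients are enrolled at any hour. Enrolment needs an in-person interview, so it follows research-staff presence under identical wording in both conditions. Screening triage lists so that nobody is missed can describe completeness within staffed sessions. About one patient per weekday per site fits a common daytime window. So do the need for an independent physician and the early disclosure of the sequence to help sites plan ({16b}). On that reading q₀ = q₁ and there is no bias from this source. Rosters are also detail that an article may leave to the full protocol, which is not shown.

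Much of this stands. A reader might infer that the two conditions do come from different hours and that the fourth objective is confounded. The documents do not support that: they give no hours for physiotherapists or research staff, and a common window fits the text.

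A reader might also infer that off-roster patients in APP periods would be seen by physicians yet counted as APP, diluting the primary outcome. That is not the plan either. {11a} has experimental-arm patients managed by a physiotherapist, and {20a} plans a per-protocol analysis beside intention-to-treat.

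What remains is narrower. The article does state a recruitment frame, that frame has no hours limit, and it sits beside a provider capacity that cannot match it around the clock. If sites already use a common window, the recruitment wording should say so. General adjustment for observed baseline differences is no substitute, because arrival time is not among the listed variables.

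**Conclusion.** The point holds as a conditional risk. The wording permits control patients to be enrolled over wider hours than APP patients. If that happens, the cluster and period effects leave the whole resulting shift in the intervention estimate for wait and length of stay. The bias is the difference in off-hours share times the off-hours difference in the outcome. Its size cannot be known from the article: it is zero with a common window, and 3 to 30 minutes for q from 0.1 to 0.5 and D from 30 to 60 minutes, all assumed values. The demonstrated consequence is confined to the fourth objective; no claim is made about the primary endpoint (BPI interference at 4 weeks), and the sample size is unaffected. The change is worth making because it costs little and works best if settled before recruitment begins.

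**What to change.** In Recruitment {15}, state one recruitment window per site, in days and hours. Set it before the first period from the planned physiotherapist roster and apply it identically in all four periods, control included. Limit the statement about omitting no patients to that window.

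In Statistical methods {20a}, prespecify arrival shift and weekday/weekend as fixed effects in the wait and length-of-stay models, using the arrival time already needed to compute wait. The window is the main remedy. Adjustment handles imbalance within it, but cannot show how APP care performs in hours when no APP patients were enrolled.

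The cost is some protocol wording, a roster-based timetable and two model terms. Fewer control-period patients would be eligible, but with about 5 per site per week needed, that loss should be small.

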### Assignment of interventions: allocation

#### Sequence generation {16a}

All eligible and consenting sites will be randomly assigned to a sequence of models of care (APP-led or usual). All sites will begin the trial with a baseline period where no site is in the intervention arm. Then, during 6-week intervals, two sites (clusters) will move to the intervention arm with this timing randomized at the outset of the trial. After the third step in the sequence, all six sites will be in the intervention arm.

#### Concealment mechanism {16b}

Sites will be informed at the beginning of the trial of the intervention sequence as this will allow efficient planning of the intervention arm at each ED.

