### Assignment of interventions: blinding

#### Who will be blinded {17a}

Neither participants nor providers will be blinded in this study in the context of this pragmatic RCT. Even if the patient’s perception can be influenced by the type of provider they see, this approach is necessary because of the pragmatic nature of the proposed care model, and it is important that patients know which provider and models of care they are exposed to as this increases the external validity of the current trial. An independent statistician not involved in any other parts of this trial and blinded to the participants’ allocation will conduct the statistical analyses.

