## Statistical methods

### Statistical methods for primary and secondary outcomes {20a}

Descriptive statistics will be used to present the participants’ characteristics. Baseline demographic data will be compared across groups and the participating EDs to establish the comparability of study samples across intervention arms and clusters. If differences are observed, statistical models will be adjusted, and any difference will be considered. Descriptive statistics will be computed for all outcome measures at different measurement times. Per-protocol and intention-to-treat analysis will be performed. Outcomes will be analyzed at the individual level using mixed models as recommended for stepped-wedge designs [56]. A linear mixed model with a random effect for cluster and fixed effects for the intervention status and time period will be used for continuous outcomes including the primary outcome (BPI score). Separate analyses will be conducted on each of the secondary outcomes. In the case of non-normal outcomes, including re-visits and adverse events, a generalized linear mixed-model framework will be used. Time-driven activity-based costing (TDABC) will be the methodology used to capture the costs of providing services to achieve primary and secondary outcomes. TDABC’s micro-costing approach will allow us to precisely determine and differentiate the cost of providing care based on the specific types of patients. Measuring patient outcomes and costs to achieve those outcomes will provide a more rigorous approach to understanding the value of introducing innovative modifications to existing clinical pathways. This approach has the potential to compare costs, outcomes, and clinical pathways within single health care institutions, among regional care centers and across provinces.

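### Patients are recruited after cluster randomisation by staff who can know the current arm, yet baseline BPI adjustment of the primary model depends on whether imbalance is observed

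*Protocol article*

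**What the plan says.** All references are to the protocol article.

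- **Sequence generation {16a}:** after a common control period, "two sites (clusters) will move to the intervention arm with this timing randomized at the outset of the trial".
- **Concealment mechanism {16b}:** "Sites will be informed at the beginning of the trial of the intervention sequence". The reason given is planning of the intervention at each ED.
- **Recruitment {15}:** patients are enrolled after that. "Eligibility of ED patients will subsequently be assessed regarding the inclusion and exclusion criteria during an in-person interview with a research professional", with review of medical records. "Research professionals will explain the study to eligible patients and obtain their informed consent". All new patients triaged as a possible MSKD are considered, triage lists are screened for missed patients, and limited data are kept on decliners.
- **Who will be blinded {17a}:** "Neither participants nor providers will be blinded in this study in the context of this pragmatic RCT". Only the statistician is described as blinded.
- **Intervention description {11a}:** "Participants in both arms presenting a non-MSKD condition after assessment will be excluded from the study". These exclusions and their reasons are to be analysed by group.
- **Table 1:** BPI is collected in the enrolment column, which precedes the allocation column.
- **Statistical methods {20a}:** the model for the 4-week BPI has a random cluster effect and fixed effects for intervention status and period. Baseline data are compared across arms and EDs, and then: "If differences are observed, statistical models will be adjusted, and any difference will be considered".

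**The concern.** In a stepped-wedge trial with individual consent, randomising the clusters does not by itself balance the patients. Balance also requires that the same kinds of patient enter under both models of care. Here the people who judge whether a disorder is minor, or whether a red flag is present, can know which model their site is running. The target of 31 patients per site in six weeks is about 0.7 a day (31/42). If more patients than that are eligible, staff have some discretion over whom to approach.

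If patients enrolled under APP care start with better or worse pain interference, part of that gap carries through to the self-reported 4-week BPI and is read as a treatment effect. The most direct analytic defence is a baseline BPI term, and the data for it are already collected. The plan includes it only if a difference is seen, without saying which variables are eligible or how a difference is judged. That leaves the primary model to be settled after the data are in hand.

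**Working it through.** **1. The plan's own figure.** Inputs from Sample size {14} and Trial design {8}: I = 6 clusters, T = 4 periods, two clusters switching at each of three steps, m = 27 evaluable per cluster-period, ICC 0.004, effect 0.35 SD, two-sided 5%. Hussey-Hughes variance with total variance 1:

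- σ² = (1 − 0.004)/27 = 0.03689; τ² = 0.004
- U (treated cells) = 12; W (sum of squared period totals) = 0 + 4 + 16 + 36 = 56; V (sum of squared cluster totals) = 2(9 + 4 + 1) = 28
- Var = Iσ²(σ² + Tτ²) / [(IU − W)σ² + (U² + ITU − TW − IV)τ²]
- Numerator: 6 × 0.03689 × 0.05289 = 0.01171
- Denominator: 16 × 0.03689 + 40 × 0.004 = 0.7502
- Var = 0.01560, SE = 0.1249 SD
- Power = Φ(0.35/0.1249 − 1.96) = Φ(0.842) = 0.800

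The stated 27 per cell and 80% power reproduce, and 31 × 4 × 6 = 744.

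**2. Effect of a baseline gap if unadjusted.** The documents give neither a baseline gap nor a correlation, so both are assumed. If arms differ by b SD in baseline BPI, and baseline correlates ρ with the 4-week score, bias = ρb. Type I error = P(Z > 1.96 − bias/SE) + P(Z < −1.96 − bias/SE).

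| b (SD) | ρ | Bias (SD) | Share of 0.35 | Type I error | Power if bias opposes a true 0.35 |
|---|---|---|---|---|---|
| 0.10 | 0.3 | 0.03 | 9% | 5.7% | 73% |
| 0.10 | 0.5 | 0.05 | 14% | 6.9% | 67% |
| 0.10 | 0.7 | 0.07 | 20% | 8.7% | 61% |
| 0.20 | 0.3 | 0.06 | 17% | 7.7% | 64% |
| 0.20 | 0.5 | 0.10 | 29% | 12.6% | 52% |
| 0.20 | 0.7 | 0.14 | 40% | 20.2% | 39% |

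Over gaps of 0.05 to 0.30 SD and correlations of 0.3 to 0.7, bias runs from 0.015 to 0.21 SD and type I error from 5.2% to 39%.

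**3. Would the conditional rule catch such a gap?** The plan does not say how a difference is judged. Suppose it were a 5% test on the 31 recruited per cell.

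- In a model like the primary one (same ICC assumed for baseline BPI), SE = 0.1173. The expected z for a 0.20 SD gap is 0.20/0.1173 = 1.71, below 1.96.
- In a crude comparison of 12 × 31 = 372 patients per arm, SE = √(2/372) = 0.0733. The expected z is 0.10/0.0733 = 1.36 for a 0.10 SD gap and 0.20/0.0733 = 2.73 for 0.20 SD.

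So whether a relevant gap triggers adjustment depends on a choice of comparison that is not fixed.

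**4. What prespecified adjustment gains.** With ρ = 0.5, and the same proportional reduction within and between clusters, residual variance is multiplied by 1 − 0.25 = 0.75. SE = 0.1249 × √0.75 = 0.108. Power = Φ(0.35/0.108 − 1.96) = Φ(1.28), about 90%, at the same sample size.

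**The case against.** The strongest reply is that this is an openly unblinded pragmatic trial. A stepped wedge usually has to tell sites when they switch, and the plan gives a planning reason for doing so. The current arm is visible from who is on shift, so withholding the later sequence would leave the main route open. That stands, and it is why disclosure itself is not the fault.

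The plan also has real safeguards: every new patient with a possible MSKD is considered, triage lists are re-screened, post-assessment exclusions are analysed by group, and baseline comparison across arms and clusters is systematic. These can reduce or reveal selection. They do not mask the eligibility judgement or the consent conversation. The decliner items listed include no BPI score.

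A reader might infer that patients accept, decline and rate their baseline pain already knowing their provider. The documents do not say so. Section {17a} says only that participants are unblinded and should know the provider they are exposed to, while Table 1 places consent and baseline BPI before allocation. That order does not prove patients are unaware, since allocation is by site.

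A reader might also infer that decliners are compared with participants only overall. Section {15} neither says this nor rules out a breakdown by arm.

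**Conclusion.** The point holds as a weakness in how the primary analysis is fixed, not as proof of biased enrolment. Recruitment after randomisation by staff who can know the arm makes a gap in case mix plausible, and the named model contains no baseline term unless a loosely defined check calls for it.

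The size is illustrative. At an assumed correlation of 0.5, baseline gaps of 0.10 and 0.20 SD give bias of 0.05 and 0.10 SD and type I error of about 6.9% and 12.6% if unadjusted. The direction is unknown, and no figure stated in the plan becomes wrong. It would be too strong to say that a baseline gap passes one-for-one into the effect, because it is scaled by the correlation. It would also be too strong to say that nothing later could correct it, since the plan does allow adjustment for differences that are seen.

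The change is worth making even if no selection occurs, because it also gains precision. Selection on unmeasured factors would remain.

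**What to change.** **In {20a}**, replace the conditional sentence with a fixed rule: the 4-week BPI model includes baseline BPI interference, CTAS level, affected body area and symptom duration as fixed effects, together with the cluster, intervention and period terms, whatever the observed balance. Report the model without these covariates as a sensitivity analysis.

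**In {15}**, as a supporting step, state that eligibility, consent and baseline BPI are completed before the patient is told which provider they will see, consistent with the order in Table 1. This also keeps the baseline score a valid covariate, because it cannot then be coloured by knowing the provider. Report screened, eligible and consented proportions by arm within period, using the triage-list screening and decliner data already planned.

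**In {16b}**, nothing need change; sites can still be told their sequence.

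**Cost:** one analysis sentence and a site instruction. All four covariates are already collected at inclusion, there are no extra visits, and the sample size is unchanged. Patients still learn their provider before care, so the pragmatic rationale in {17a} is kept. The limit is that recruiters can still see which model is running, so protection is partial.
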